### Participants

Participants will be recruited via flyer and email advertisement and all interventions will be undertaken at the University of Sydney. The participant’s caregivers will be asked to provide informed consent for a child to participate prior to admission into the study in accordance to our ethics approval.

Inclusion criteria will be: a) clinical diagnosis of suspected CAS, b) between 4 and 12 years of age, c) comprehension skills within 1 SD of the mean for a child’s chronological age (based on normative data for the receptive language score from the Clinical Evaluation of Language Fundamentals (CELF) - Fourth edition or CELF Preschool - Second edition [45,46], d) normal or adjusted-to-normal hearing and vision, e) the child and at least one parent as native Australian English speakers, and f) no other diagnosed developmental/genetic disorders.

### Assessment process

#### Screening

All potential participants will be screened over the phone and by requesting any speech pathology or other relevant reports to determine if children are likely to meet the inclusion criteria. Any overt contraindications should be determined at this time (e.g. other developmental diagnoses).

#### Eligibility assessment

All potential participants who are not excluded during telephone screening will participate in a two-hour assessment to ensure they meet the inclusion criteria and meet the diagnostic criteria for CAS. The current gold standard in CAS diagnosis is expert clinical opinion as there are no validated standardised assessments available [13]. Accordingly CAS diagnosis will be made by the first author according to the ASHA (2007) criteria [1] as well as Strand’s 10 point checklist [47] where each of the ten items are assessed across three tasks and a diagnosis of CAS is made if a child scores four or higher on the checklist. Diagnoses will be verified by the second author blinded to the first author decision.

The eligibility assessment includes a case history questionnaire, hearing screening [48], the CELF [45,46] to determine age appropriate comprehension skills, completing three repetitions within the Inconsistency subtest of the Diagnostic Evaluation of Articulation and Phonology (DEAP) [49] to determine percentage within-word consistency across 25 words, the Test of Polysyllables [50,51] to document phonemic and phonetic level errors in words with greater complexity, a 100-utterance connected speech sample [52] and an oral structural and functional examination [53].

#### Diagnostic assessment

Eligible participants will undergo a further two hours of assessment to describe their broader communication skills. The further assessment will test memory and processing skills using the Children’s Test of Nonword Repetition [54], Comprehensive Test of Phonological Processing [55], Test of Auditory Processing Skills (3^rd^ edition) [56] (verbal memory, auditory discrimination); processing and production of prosody using the PEPS-C Test of Prosody [57]; and severity of articulation disorder using the Goldman-Fristoe Test of Articulation - Second edition (GFTA-2) [58]. Finally, an estimate of verbal cognitive ability will be obtained with the Peabody Picture Vocabulary Test – 4 [59,60] .

#### Baseline assessment probe

One further hour of assessment will be undertaken using a specially designed probe of 292 single sounds, words and phrases using a PowerPoint presentation to establish baseline performance on treated and untreated experimental stimuli. The first 162 stimuli are the Nuffield Dyspraxia Programme’s Dyspraxia Assessment stimuli [41] consisting of a variety of single consonants (e.g. ‘s’ or ‘d’), vowels (e.g ‘ah’ or ‘oo’), one syllable words (e.g. ‘no’, ‘up’ and ‘moon’), two syllable words (e.g. ‘dinner’ and pocket’), multisyllable words (e.g. ‘banana’ and ‘caterpillar’), words with clusters or blends (e.g. ‘**st**ar’ or ‘fa**st**’) and phrases (e.g. ‘do you like jelly?’ and ‘I saw five camels at the zoo’). In addition, 80 nonsense words will be probed as stimuli for the ReST program, with 40 designated as treatment stimuli and another 40 as untreated stimuli. Each set of 40 words will be individualized based on the child’s speech skills and stimulus selection criteria for the ReST programme. Twenty will be at the child’s current level (e.g. two syllable CVCV words e.g. ‘tegar’) and the other twenty will be the related next step (e.g. ‘tegarfer’) to allow for assessment of treatment gains if progression criteria are met in the intervention period. The final component of the probe will be 50 untreated words of one, two and three syllables to measure potential generalisation of treatment effects to untreated speech behaviours for both treatments. All real words will be pictured and written on screen. All ReST stimuli will be written on screen. Participants with adequate reading skills will read the pseudo-word stimuli, those who cannot read will be asked to imitate a model. A pre-recorded model of all stimuli said by one Australian English speaker will be available to ensure consistency in delivery across examiners if imitation is required. The PowerPoint presentation will also include built in standardised breaks and animations to promote interest and motivation for the participants. Each participant will have individualised stimuli chosen for them for both programmes based on their assessment performance prior to randomisation, group allocation and treatment.

### Group allocation

Participants will be consecutively allocated a participant number from 1–30. Participants will be randomised to treatment condition utilising concealed allocation. That is, cards with treatment name (ReST or NDP3) will be placed in opaque envelopes, an independent person will then randomly draw envelopes and consecutively place participant numbers 1 to 30 on the front of the envelopes without opening them. In this way, each eligible participant will be randomly allocated to treatment according to their assigned participant number.

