**Methods/Design:**

A parallel group, fixed size randomised control trial will be conducted in Sydney, Australia to determine the efficacy of two treatments for Childhood Apraxia of Speech: 1) Rapid Syllable Transition Treatment and the 2) Nuffield Dyspraxia Programme – Third edition. Eligible children will be English speaking, aged 4–12 years with a diagnosis of suspected CAS, normal or adjusted hearing and vision, and no comprehension difficulties or other developmental diagnoses. At least 20 children will be randomised to receive one of the two treatments in parallel. Treatments will be delivered by trained and supervised speech pathology clinicians using operationalised manuals. Treatment will be administered in 1-hour sessions, 4 times per week for 3 weeks. The primary outcomes are speech sound and prosodic accuracy on a customised 292 item probe and the Diagnostic Evaluation of Articulation and Phonology inconsistency subtest administered prior to treatment and 1 week, 1 month and 4 months post-treatment. All post assessments will be completed by blinded assessors. Our hypotheses are: 1) treatment effects at 1 week post will be similar for both treatments, 2) maintenance of treatment effects at 1 and 4 months post will be greater for Rapid Syllable Transition Treatment than Nuffield Dyspraxia Programme treatment, and 3) generalisation of treatment effects to untrained related speech behaviours will be greater for Rapid Syllable Transition Treatment than Nuffield Dyspraxia Programme treatment. This protocol was approved by the Human Research Ethics Committee, University of Sydney (#12924).

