## Methods and design

A parallel group, fixed size randomised control trial will be conducted in Sydney, Australia to determine the comparative efficacy of two treatments for Childhood Apraxia of Speech: the Rapid Syllable Transition Treatment (ReST) and the Nuffield Dyspraxia Programme – Third edition (NDP3). This protocol has been approved by the Human Research Ethics Committee of the University of Sydney (approval number 12924).

A power calculation has been used to determine the number of participants to be recruited. Previous pre and post treatment data from within-subject ReST studies (e.g. [12,16]) for a total number of 14 participants demonstrated statistically significant differences for 12 of the 14 participants and large effect sizes (Cohen’s d = 1.36). Based on this, the estimated sample size to detect a reliable treatment effect (alpha level 0.05, beta level 80%) is 6 per group for this RCT. We have no estimates for the NDP3 due to lack of published effect sizes or data to enable calculation of an effect size. On this basis we propose 10 per group to allow for attrition and to accommodate the higher heterogeneity with a between-subjects design.

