### Intervention delivery and dosage

The two treatments will be conducted in parallel within three treatment blocks over school holiday time in Sydney, Australia, permitting a maximum of 10 participants per block to allow for recruitment of between 20 and 30 participants across 3 treatment blocks. Treatments will be delivered by trained and supervised speech pathology clinicians. Each child will be allocated one clinician for all treatment sessions. Clinicians will be blinded to hypotheses. The parents of children will not be informed of the name and strategies of the treatment their children are receiving until after data collection is completed to ensure no home practice will be attempted.

All participants, regardless of treatment condition, will receive the same amount of time in treatment with 1-hour sessions, four times a week for three weeks for a total of 12 treatment hours. All participants will complete between 100–120 production trials on treatment words per 1-hour session (i.e. a total of 1200 to 1440 responses during treatment), to match the practice intensity and session distribution of our pilot studies of ReST [12,16] and the current best evidence of treatment intensity for CAS [61]. For the NDP3 programme this will equate to approximately 30–40 trials during each 18 minute period for each goal. For the ReST programme, this will equate to 5–20 Pre-Practice trials and 100 practice trials.

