### Potential limitations

As this is a behavioural treatment, it is not possible to blind clinicians and participants to treatments as per CONSORT [66] and PEDro guidelines [67]. Even though parents will not be told the name or details of the treatment their child will receive until their participation has ended, they could still talk to another parent in the waiting room and realise the treatments are different.

Clinicians will conduct all treatment sessions with two assigned participants using the ReST treatment for one and the NDP3 treatment for the other. Thus they will be required to be trained in and deliver both treatments. This is to reduce potential clinician effects. There is potential for drift across methods, motivating supervision of sessions by the authors and calculation of treatment fidelity on a portion of all treatment sessions.

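### A single draw of 30 envelopes, unrestricted by holiday block or clinician, does not guarantee the one-ReST-one-NDP3 caseload per clinician on which the design relies

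*Protocol article*

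**What the plan says.** **Allocation.** Under Group allocation, "cards with treatment name (ReST or NDP3) will be placed in opaque envelopes"; then "an independent person will then randomly draw envelopes and consecutively place participant numbers 1 to 30 on the front of the envelopes". As a result "each eligible participant will be randomly allocated to treatment according to their assigned participant number". The number of cards for each treatment is not stated, and neither holiday block nor clinician enters the procedure.

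**Delivery.** Intervention delivery and dosage sets three school-holiday blocks, "permitting a maximum of 10 participants per block to allow for recruitment of between 20 and 30 participants across 3 treatment blocks", and gives each child a single clinician throughout.

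**Caseload.** Potential limitations states: "Clinicians will conduct all treatment sessions with two assigned participants using the ReST treatment for one and the NDP3 treatment for the other". The reason follows: "This is to reduce potential clinician effects".

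**Size.** Methods and design says "we propose 10 per group to allow for attrition and to accommodate the higher heterogeneity with a between-subjects design". The Abstract says "At least 20 children will be randomised to receive one of the two treatments in parallel".

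**The concern.** The allocation rule makes treatment depend on participant number alone. The caseload rule needs as many ReST as NDP3 children among those whom the clinicians share out. If a clinician's two children are treated in the same holiday block, that means equal numbers in every block, and the described draw does not produce this.

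When a block comes out uneven, two outcomes are open. Some clinicians treat two children on the same treatment, and for them the comparison is no longer made within clinician. Or someone moves a child to restore the pairs and so departs from the drawn sequence, which weakens the concealed randomisation that a trial of 20 to 30 children depends on. The article does not say which rule gives way. The question could arise in the first block.

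**Working it through.** **Inputs.** From the document: envelopes numbered 1 to 30; at most 10 children per block; 3 blocks; 20 to 30 children; two children per clinician, one per arm; target 10 per group; d = 1.36; alpha 0.05; 80% power. Assumed, because not stated: 15 ReST and 15 NDP3 cards. The alternative shown is independent 50:50 cards.

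**1. The plan's own size.** The stated 6 per group lies between the paired t-test results at d = 1.36: 5 one-sided, and 6.4 (so 7) two-sided. It was raised by judgement to 10 per group. A two-sided two-sample t-test with 10:10 and d = 1.36 has power 0.820, which is the reference for step 5. That d is a within-subject figure; it is used here only to put a price on imbalance.

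**2. Pairs within the same block, 15+15 cards, full blocks of 10.**
- First block 5:5: C(15,5)² / C(30,10) = 3003² / 30,045,015 = 0.300.
- Second block 5:5, given the first: C(10,5)² / C(20,10) = 252² / 184,756 = 0.344.
- The third is then 5:5 with certainty, so all three: 0.300 × 0.344 = 0.103. The same figure applies to 20 children in two full blocks.
- With k ReST children in a block of 10, |k − 5| of the five clinicians cannot have one child per arm, however clinicians are assigned afterwards. The mean of |k − 5| is 1.00.

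**3. The same with independent 50:50 cards.**
- One block 5:5: C(10,5) / 2¹⁰ = 252 / 1024 = 0.246.
- All three: 0.246³ = 0.015.
- Mean number of unpaired clinicians per full block: 5 × 252 / 1024 = 1.23.

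**4. Pairs allowed to span blocks.** Only equal totals are then needed.

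| Children enrolled | 15+15 cards | Independent 50:50 |
|---|---|---|
| 20 | C(15,10)² / C(30,20) = 0.300 | 0.176 |
| 30 | 1 | 0.144 |

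**5. Consequence for group size, 15+15 cards.**
- At 20 enrolled, an arm falls below 10 with probability 1 − 0.300 = 0.700, and the split is 8:12 or worse with probability 0.245.
- An arm falls below 10 with probability 0.215 at 22 and 0.017 at 24. From 25 it cannot happen, because one arm can hold at most 15 and 25 − 15 = 10.
- Power at 20 children: 0.820 at 10:10, 0.816 at 9:11, 0.804 at 8:12, 0.783 at 7:13. Weighted by the probability of each split, it is 0.813, a loss of 0.007.

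**The case against.** The article is condensed. It neither gives the card counts nor says that the envelopes were left unsorted by block; a fuller document might hold a restriction. It also does not say that a clinician's two children must be in the same block, and if they need not be, the figures in step 2 do not apply. The stated aim is to reduce clinician effects, and with about four of five clinicians still paired it would be partly met. An independent person numbers the envelopes unopened, so the idea that staff would move children is conjecture.

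Much of this stands, and it limits the wording. A reader might infer that the two rules cannot both be followed. The document does not support that: under 15+15 cards with same-block pairing, both hold about one time in ten, and with pairs spanning blocks they always can at 30 children. A reader might also infer that the trial will miss 10 per group. That is a risk only near 20 enrolled, and it costs under one point of expected power. Nor should the 20 to 30 range, in a trial described as of fixed size, be read as stopping on results: the article ties the range to block capacity and describes no interim look.

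What does not fall away is the mismatch itself. The procedure is set out step by step as one draw, and the caseload rule is stated as applying to every clinician. Unwritten detail could reconcile them, but the text as it stands does not.

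**Conclusion.** The point holds as a lack of guarantee. The allocation described does not secure the clinician pairing that the article offers as its protection against clinician effects.

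If pairs are within block and the three blocks are full, pairing is incomplete somewhere with probability 0.90 (1 − 0.103) under 15+15 cards, or 0.985 (1 − 0.015) under independent cards. About one clinician in five per full block is affected under 15+15. If pairs may span blocks, the problem disappears at 30 children with 15+15 cards, but complete pairing at 20 still has probability only 0.30. These figures rest on the assumed card counts, on full blocks and on which pairing rule applies. Unequal group size is a minor side effect. The case for change rests on the pairing and on protecting the drawn sequence.

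**What to change.** Randomise within each holiday block. The simplest form is one ReST and one NDP3 card per clinician pair, in opaque envelopes shuffled by the independent person. Open them only after every child in that block is enrolled, has completed baseline and has been assigned to a pair. The timing matters: once one child's arm is known, the other's follows.

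A balanced set of cards over the whole block also works. In that form the pairs have to be made up from one child per arm after opening, preferably by a further random draw.

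Blocks have a maximum of 10, not a fixed number. Where a block has an odd number of children, allocate the unpaired child by a random card. With this scheme a full block always splits 5:5, two full blocks give 10:10, and every clinician with two children has one per arm.

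Include treatment block (or pair) as a factor in the analysis. Three blocks use 2 degrees of freedom. Pair would use more (9 with ten pairs), so block is the cheaper choice.

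The cost is re-sorting envelopes before the trial starts, those few degrees of freedom, and the need to enrol children as a block before envelopes are opened, which holiday delivery largely implies already.

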### Intervention delivery and dosage

The two treatments will be conducted in parallel within three treatment blocks over school holiday time in Sydney, Australia, permitting a maximum of 10 participants per block to allow for recruitment of between 20 and 30 participants across 3 treatment blocks. Treatments will be delivered by trained and supervised speech pathology clinicians. Each child will be allocated one clinician for all treatment sessions. Clinicians will be blinded to hypotheses. The parents of children will not be informed of the name and strategies of the treatment their children are receiving until after data collection is completed to ensure no home practice will be attempted.

All participants, regardless of treatment condition, will receive the same amount of time in treatment with 1-hour sessions, four times a week for three weeks for a total of 12 treatment hours. All participants will complete between 100–120 production trials on treatment words per 1-hour session (i.e. a total of 1200 to 1440 responses during treatment), to match the practice intensity and session distribution of our pilot studies of ReST [12,16] and the current best evidence of treatment intensity for CAS [61]. For the NDP3 programme this will equate to approximately 30–40 trials during each 18 minute period for each goal. For the ReST programme, this will equate to 5–20 Pre-Practice trials and 100 practice trials.

#### Nuffield Dyspraxia Programme – Third edition (NDP3)

We have operationalised the NDP3 programme with the assistance of its original authors to ensure dosage and other aspects will be controlled with the other treatment and yet we will be faithful to the original programme. Therapy will be conducted in accordance with the tenet of the NDP3 and the operationalised manual which was developed for this study, and treatment fidelity will be evaluated to ensure compliance.

##### Treatment goals and stimuli

In the NDP3, treatment goals are selected through assessment of a child’s speech sound, melody (prosody), vocal and nasal quality strengths and needs. Three independent goals will be selected according to the NDP3 hierarchy ‘Treatment Planning and Progression’ checklist in the original manual [41] with the intention of building on their strengths to facilitate learning of a new speech pattern or incorporate an old pattern or sound into a new more complex context (e.g. a two rather than one syllable word). Each of the three individualised goals will involve the child naming five different pictured stimuli independently with 90% accuracy. Cues are provided as needed but only independent productions over at least 12 opportunities are counted towards achieving the goal.

Five sounds or real word stimuli will be chosen per goal (for example if the goal is ‘single consonant sounds’, initially selected stimuli will include sounds the child can produce at least 10%–60% of the time with cues but would benefit from therapy (e.g. ‘s’, ‘h’ ,‘f’, ‘m’ and ‘y’). The original NDP3 pictured stimuli will be used in sessions [41]. Non-speech (oral-motor) goals will be excluded from this study to ensure consistent dosage of speech production intervention across treatments within each treatment session.

##### Treatment procedure

Each of the three goals will be worked on in a block of 18 minutes during every session using game activities. Each treatment task will incorporate verbal instructions, modelling, articulation, visual-tactile cues to guide tongue/lip placement (e.g. cued articulation [62]) and pictured stimuli to guide children in modifying their production to say the sound or selected stimuli accurately. Immediate feedback describing the child’s performance (e.g. ‘You made a great ‘s’ sound with your teeth together!’) will be given after every production attempt (i.e. on 100% of responses). When a production is accurate, the child will be asked to repeat the stimulus item stimuli three times to help consolidate new motor plans. The child will need to say each stimulus item with 90% accuracy out of at least 12 trials without modelling or cueing from the clinician before it is removed from treatment and a new target word is introduced. Production accuracy for the acquired word(s) will be probed at the start of each goal every second session to ensure maintenance of skill. If performance deteriorates, it will be re-introduced into the set of treatment words and the newest item removed to maintain the same number of treatment words at all times. Once 5 stimulus items are acquired for a given goal, treatment will move up the hierarchy to the next level (e.g. once a consonant-vowel (CV) syllable is achieved, consonant-vowel-consonant-vowel (CVCV) sequences using the same speech sounds will be targeted).

